### Collection of Fecal Samples

Fecal samples from 80 SCC patients will be collected at the onset and end of the treatment. Healthy volunteers will submit to only 1 stool collection (at baseline). Participants should be advised to maintain a normal diet (with no special changes compared with previous habits) in the run-in phase and avoid spicy, greasy, or probiotics-containing foods (such as yogurt) before stool samples are collected. Patients will receive a teaching video, as well as detailed written and oral instructions on how to collect feces using the Longsee fecal microbial genome protection solution kit (Guangdong Nanxin Medical Technology Co., Ltd.). Collection of two tubes of feces each time is required for the detection of intestinal microbiome and microRNAs. The collection location can be chosen at home or in the hospital according to the preferences of the participants. After collecting the inside of the middle part of the feces (about 3 g), it will be immediately transferred to the −80°C refrigerator in the hospital or temporarily stored in the 4°C refrigerators at home, and then quickly transferred to the researchers for microRNAs and gut microbiota analysis within 24 h.

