Intestinal microbiota plays a critical role in GI transit. Following the onset of SCC, in addition to the decreased richness and diversity of the intestinal microbiome, microbial metabolites vary greatly (17). For example, metabolites short-chain fatty acids and γ-aminobutyric acid decrease, leading to reduced expression of the colonic serotonin transporter and intake of 5-hydroxytryptamine (5-HT), which weakens intestinal motility (18). Additionally, intestinal neuroendocrine factors may also be changed through the release of bacterial endotoxin lipopolysaccharide and bacterial final metabolites, resulting in the aggravation of constipation symptoms (19, 20). In a previous study, we have demonstrated that acupuncture could affect the production and degradation of short-chain fatty acids mainly by promoting the recovery of intestinal microbiome, thus stimulating the neural signal transduction of 5-HT signal pathway (21). Besides, acupuncture was found to be lesser effective when the intestinal microbial community was dysregulated by antibiotics (22). Nevertheless, the behind mechanism has not been clarified yet.

MicroRNA (miRNA) is a kind of endogenous, non-coding single-stranded RNA with a length of about 22 nucleotides and is highly conserved during evolution (23). It is proven that miRNA along with its related networks is involved in the imbalance of intestinal microbiota, which is the key to the pathogenesis of functional constipation (24–27). For instance, in patients with SCC, 13 miRNAs were found to be up-regulated in colonic mucosa and were identified as biomarkers for the diagnosis of disease severity (24). The miRNAs which show differential expression patterns could cause changes in intestinal microbial metabolic pathways via targeting and regulating the transcriptional levels of related genes (25, 26). In an animal experiment, related miRNA deficiency was highly likely to cause intestinal microbial disorders, while fecal miRNA transplantation could reshape the microbiota and alleviate gastrointestinal symptoms (27).

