#### Inclusion Criteria

Participants meeting all the following conditions will be enrolled in this study:

Aged 18 to 60 years old;History of SCC for a minimum of 6 months before the screening visit, and the activity of symptoms last for at least 3 months;Two or fewer CSBMs per week, exertion in defecation, and lumpy or hard stools (Bristol Stool Form Scale [BSFS] ≤3) during the run-in period;No special eating habits and not accompanied by severe anxiety, depression, or other mental disorders (SAS or SDS score <75);No use of medicine for constipation during the 1 week before enrolment (except for rescue medicine), including intestinal microecological preparations, probiotics, etc.; no acupuncture treatment for constipation in the previous 1 month; no participation in any other ongoing trial;Volunteered to join this trial and signed the informed consent.

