### Intervention

The Park Sham Placebo Acupuncture Device (PSD) will be used, plus a disposable sterile acupuncture needle (length 25–75 mm, diameter 0.30 mm) for the VA group and a disposable sterile retractable blunt needle with the same size for the sham acupuncture group.

All subjects will be assigned to receive acupuncture treatments for 16 times within 4 weeks, including 5 times a week on working days for the first 2 weeks, and 3 times a week (once every other day) on working day for the last 2 weeks. The operators should be acupuncturists with a certificate to practice and at least 5 years of professional qualification.

Other medications will not be allowed, except that bisacodyl (5–10 mg) and glycerin enema (110 ml) can be used for participants who fail to have a bowel movement for 3 or more consecutive days. If the patient does not respond to bisacodyl (5–10 mg) and glycerin enema, 1–2 tablets (5–10 mg) of enteric-coated bisacodyl will be permitted (11). Furthermore, the date, specific time, dose of bisacodyl or glycerin enema using will be recorded in the defecation diary and case report form (CRF).

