#### MicroRNAs High-Throughput Sequencing Analysis

High-throughput sequencing using stool samples will be performed for miRNA expression profiling to determine candidate miRNA biomarkers for the efficacy of acupuncture (24–26). Fecal miRNA levels initially will be determined using a TaqMan low-density array in pooled samples. Markedly altered miRNAs in participants will subsequently be validated using quantitative real-time polymerase chain reaction on individual samples. Agilent 2100 will be used for detection, and after qualification, these fragments will be sequenced using the Illumina NOVA platform. Bowtie software will be employed to classify and annotate sRNA, and unannotated reads will be obtained by comparing clean reads with the database. The difference between SCC patients and healthy volunteers at baseline will be analyzed to explore potential biomarkers associated with the development of SCC. Within the pool of biomarker candidates related to SCC, the difference between VA and SA at week 4 will be compared, to determine biomarkers related to the clinical efficacy.

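### Nothing keeps a stool produced by rescue laxative or enema from being sequenced, so the patient-versus-healthy biomarker contrast mixes constipation with rescue use

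*Protocol article*

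**What the plan says.** All places are in the protocol article.

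- **Sampling.** Collection of Fecal Samples: "Fecal samples from 80 SCC patients will be collected at the onset and end of the treatment". Healthy volunteers give one sample. Participants are told to keep their normal diet in the run-in and to "avoid spicy, greasy, or probiotics-containing foods (such as yogurt) before stool samples are collected". The section also fixes the kit, tubes, quantity, storage and transfer time. It says nothing on rescue medicine.
- **Washout.** Inclusion Criteria: "No use of medicine for constipation during the 1 week before enrolment (except for rescue medicine), including intestinal microecological preparations, probiotics, etc".
- **Rescue in the trial.** Intervention: bisacodyl and glycerin enema "can be used for participants who fail to have a bowel movement for 3 or more consecutive days". Date, time and dose go into the diary and CRF.
- **Clinical outcome.** Primary Outcome Measurement counts a movement as spontaneous only if no rescue or other aid was used in the preceding 24 h.
- **Use of the samples.** MicroRNAs High-Throughput Sequencing Analysis compares patients with healthy volunteers at baseline to form a candidate pool. Within that pool, "the difference between VA and SA at week 4 will be compared, to determine biomarkers related to the clinical efficacy". miRNA levels are first measured in pooled samples. None of the three omics sections excludes, stratifies or adjusts for recent rescue.
- **Timing.** Table 1 marks the microbiota and microRNA analyses at Week −1 and Week 4, with none at Week 0. The sampling section places the first collection at the onset of treatment.
- **Antibiotics.** Neither eligibility list names them, although the Introduction says "acupuncture was found to be lesser effective when the intestinal microbial community was dysregulated by antibiotics".

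**The concern.** The protocol treats a rescue-assisted movement as unfit to count as a clinical outcome, yet the same stool may be sequenced. Yogurt is barred before sampling and an enema is not. Patients enter with two or fewer complete spontaneous movements per week, so some rescue use is foreseeable.

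The exposed analysis is the baseline comparison with healthy volunteers. It is not randomized, and only one side has a rescue regimen. Any effect of bisacodyl or enema on a taxon or miRNA is then indistinguishable from an effect of constipation. For miRNAs this contrast also decides which markers go forward. Once an affected stool has been pooled, it cannot be taken out again.

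At week 4 the issue is interpretation. If rescue use differs by arm, a difference in a marker may run through rescue and not through a direct action of acupuncture on miRNAs or microbiota. The third objective, on mechanism, needs that distinction.

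**Working it through.** **Step 1: follow the stated rules.** A patient uses an enema during the week before enrolment, which the washout exemption permits, and submits the resulting stool having avoided the listed foods. No stated rule is broken. The same holds for a stool that follows permitted rescue near week 4. The gap therefore arises from rules the article states, including an exemption that names rescue medicine.

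**Step 2: size.** The plan has no figure on this point to reproduce. Group sizes are as stated: 80 patients (40 per arm) and 40 healthy volunteers. The share of affected samples, p, and the shift in a marker, s (in SD units), are assumptions. There is no true disease or acupuncture effect on the marker, and the test is two-sided at 0.05.

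For patients versus healthy volunteers:

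- Expected spurious difference: δ = p × s
- SE = √[(1 + s²p(1 − p))/80 + 1/40]
- Rejection rate = Φ(−1.96 + δ/SE) + Φ(−1.96 − δ/SE)

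Example with p = 0.30 and s = 1: δ = 0.30; SE = √(1.21/80 + 0.025) = √0.0401 = 0.200; δ/SE = 1.50; rate ≈ 32%.

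A Mann-Whitney simulation (6,000 trials per scenario) gives slightly lower values:

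| Affected baseline samples | Shift | Normal approximation | Mann-Whitney |
|---|---|---|---|
| 20% | 0.25 SD | 6% | 5% |
| 30% | 0.25 SD | 7% | 7% |
| 50% | 0.25 SD | 10% | 10% |
| 20% | 0.5 SD | 8% | 7% |
| 30% | 0.5 SD | 12% | 11% |
| 50% | 0.5 SD | 25% | 22% |
| 20% | 1 SD | 17% | 14% |
| 30% | 1 SD | 32% | 28% |
| 50% | 1 SD | 70% | 66% |

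The nominal rate is 5%. Repeat runs of the simulation differ by about one percentage point.

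**Step 3: week 4, 40 per arm.** The same approach with different shares by arm gives the chance of a significant difference that runs wholly through rescue. With equal shares it is 5%. With 10% in verum and 30% in sham it is about 7% at 0.5 SD and 12–13% at 1 SD. With 20% and 50% it is about 9–10% and 22–23%.

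**Step 4: two contrasts for miRNAs.** An miRNA must pass both. Taking the two as roughly independent at a 1 SD shift, the mildest pairing gives 0.14 × 0.12 ≈ 2% and the worst 0.66 × 0.23 ≈ 15%. The article states this two-stage selection only for miRNAs.

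**The case against.** **Unseen instructions.** Patients receive a teaching video and written and oral instructions that are not shown, and the full protocol may add rules. That is possible. But the article gives detailed sampling and washout rules, and they exempt rescue by name.

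**Size.** Nothing in the article supports 20–50% of samples being affected at one time point. Rescue requires three or more days without a movement, whereas eligibility counts only complete spontaneous movements, so a patient may have other spontaneous movements to sample. At small shifts the inflation is slight. This stands: the figures show sensitivity and are not estimates.

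**Week 4.** A reader might infer that unequal rescue use makes the verum-versus-sham result a false positive. It does not. Differing rescue use would itself follow from randomized treatment, so the comparison remains valid and only the mechanism is blurred. For the same reason, dropping affected week-4 samples from the main comparison would condition on a post-randomization variable and could introduce selection bias.

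**Antibiotics.** A reader might infer that recovery after antibiotics would pass for an acupuncture effect. The article does not support this for the comparison between arms. Randomization balances prior use on average, and Intervention says "Other medications will not be allowed, except that bisacodyl (5–10 mg) and glycerin enema (110 ml", which read literally bars antibiotics during treatment. What remains is the absence of a look-back before baseline, which matters mainly for the patient-versus-healthy contrast, and only if use differs between those groups.

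**The 24 h criterion.** It is an outcome-counting rule, and nothing shown establishes it as a washout for microbiota or miRNA. That is fair, and is why time since last rescue should be carried as data as well.

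**Conclusion.** The concern holds for rescue medicine and is strongest at baseline. Under the stated rules, the non-randomized contrast that selects candidate miRNAs can mix constipation with laxative or enema use, and pooling would make this irreversible. For one unrelated marker, with 20–50% of baseline samples affected, the false-positive rate is about 7–22% at 0.5 SD and 14–66% at 1 SD. Both inputs are assumed, so the true size is unknown and could be negligible. For miRNAs the second contrast reduces the chance that a marker unrelated to disease is finally named.

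At week 4 the conclusion is limited to interpretation of mechanism. The antibiotic gap is secondary. The conflict over when the baseline sample is taken is minor, but it determines which rescue period precedes the sample. This should be corrected before sampling starts; it does not touch the clinical primary outcome.

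**What to change.** 1. **Sampling rule.** In Collection of Fecal Samples, require where possible that each patient sample come from a movement meeting the protocol's own SBM definition. Otherwise take the next qualifying movement within a short fixed window. Flag any sample that still follows rescue, and keep flagged samples out of the pooled miRNA screen at baseline.
2. **Analysis.** Carry time since last rescue into the omics dataset, since "dose of bisacodyl or glycerin enema using will be recorded in the defecation diary and case report form (CRF" is already planned. Report rescue use by arm. Repeat the patient-versus-healthy contrast without flagged samples. At week 4 keep all samples in the main comparison, and treat any rescue-adjusted or rescue-excluded analysis as sensitivity only.
3. **Timing.** Reconcile Table 1 (Week −1) with the sampling section (onset of treatment) on when the baseline sample is taken.
4. **Antibiotics (secondary).** The investigators should set one common look-back for patients and volunteers, or record recent use and repeat the baseline contrast without those who report it.

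No change to rescue treatment itself is proposed. The cost is a small amendment. Some samples will be delayed by a few days, possibly more often in the sham arm, so collection dates should be reported by arm. The sensitivity analyses will use fewer samples.

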### Safety Evaluation

Safety will be assessed by routine blood examinations, renal and liver function examinations. These indicators will be measured during the run-in period and at the end of treatment. The adverse events caused by acupuncture will be recorded, such as bleeding, pain, hematoma, syncope, local infection, and so on. Serious adverse events related to the intervention will be reported to the key researchers and recorded in the CRF. Affected participants will withdraw from the study and apply for treatment or rescue promptly.

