**Safety assessment**
Safety of acupuncture			**×**	**×**				
Adverse event			**×**	**×**				**×**

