#### Blinding

In this study, we will apply a type of sham acupuncture device to mask verum and sham acupuncture between patients from the two acupuncture treatment groups. The participants, other than the acupuncturists, will be single-blinded to receive treatment in separate consulting rooms, with the avoidance of communications. In the meantime, the outcomes assessors and statisticians who are responsible for statistical analysis will also be masked concerning group assignments in the process of performing this study and data analysis.

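### Safety Evaluation makes causality a condition for recording adverse events and reporting serious ones, which is narrower than the unqualified row in Table 1

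*Protocol article*

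**What the plan says.** Two places in the protocol article set what is collected on safety.

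- **Safety Evaluation, clinical events.** "The adverse events caused by acupuncture will be recorded", followed by a list of examples that includes hematoma, bleeding and local infection. For serious events: "Serious adverse events related to the intervention will be reported to the key researchers and recorded in the CRF". Each sentence attaches a causal condition to recording or reporting. No sentence there provides for events regardless of cause, and none says who judges cause.
- **Safety Evaluation, laboratory tests.** "Safety will be assessed by routine blood examinations, renal and liver function examinations", and "These indicators will be measured during the run-in period and at the end of treatment". These carry no causal condition.
- **Table 1, safety assessment block.** There are two rows. "Safety of acupuncture" is marked at weeks 2 and 4. "Adverse event" is marked at weeks 2, 4 and 8 and has no qualifier.

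On masking, the Blinding section says "The participants, other than the acupuncturists, will be single-blinded", and adds that outcome assessors and statisticians are masked. The Sham Acupuncture Group section describes a blunt needle that retracts and does not enter the skin.

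**The concern.** In a sham-controlled trial, the comparator arm is what lets one learn from event rates whether the treatment causes harm. If each event must first be judged treatment-caused before it is written down, part of that information is gone before analysis, and no analysis plan can recover it.

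Three features of this trial make the filter matter.

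- Several of the named examples (bleeding, hematoma, local infection) are chiefly injuries of skin penetration, which the sham does not involve. Table 1 lists acupuncture and sham acupuncture as separate interventions, so it is not even clear that an event caused by acupuncture includes one in the sham arm.
- An event with another apparent cause, such as a reaction to the rescue medicines permitted in the Intervention section, falls outside the rule for non-serious events.
- For serious events, the relatedness judgement decides whether the event reaches the key researchers and the CRF. If that judgement is wrong, the section leaves no stated record from which it could be reviewed.

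At stake is any all-cause adverse event statement from the trial. The Introduction already cites a better safety profile than a drug comparator as an advantage of acupuncture. The primary efficacy outcome is not affected.

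**Working it through.** The plan states no adverse event rate and no safety figure, so there is nothing to reproduce. The main check is textual.

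**1. The passages side by side**

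| Item | Safety Evaluation | Table 1 |
|---|---|---|
| Adverse events | Recorded if caused by acupuncture | Unqualified row, weeks 2, 4, 8 |
| Serious adverse events | Reported and entered in the CRF if related to the intervention | No separate row |
| Acupuncture-specific safety | Not distinguished from adverse events | Own row, weeks 2, 4 |
| Blood, renal, liver tests | Run-in and end of treatment, no causal condition | Laboratory test row, weeks −1 and 4 |

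Table 1 separates acupuncture-specific safety from adverse events in general. Safety Evaluation does not. Staff working from one and staff working from the other could collect different data.

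**2. What the filter does to recorded counts (illustration; all rates are assumptions)**

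Inputs: 40 participants per arm (Trial Design: 80 randomized 1:1). Assumed: the same all-cause event proportion *p* in both arms, and the probability that an event is attributed to treatment, *a*V in verum and *a*S in sham.

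- Expected recorded per arm = 40 × *p* × *a*
- Spurious arm difference in percentage points = 100 × *p* × (*a*V − *a*S)

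| *p* | *a*V / *a*S | Recorded verum / sham, per 40 | Spurious difference |
|---|---|---|---|
| 0.10 | 0.5 / 0.5 | 2.0 / 2.0 | 0 |
| 0.10 | 0.8 / 0.4 | 3.2 / 1.6 | 4 |
| 0.10 | 0.9 / 0.2 | 3.6 / 0.8 | 7 |
| 0.20 | 0.5 / 0.5 | 4.0 / 4.0 | 0 |
| 0.20 | 0.8 / 0.4 | 6.4 / 3.2 | 8 |
| 0.20 | 0.9 / 0.2 | 7.2 / 1.6 | 14 |
| 0.30 | 0.5 / 0.5 | 6.0 / 6.0 | 0 |
| 0.30 | 0.8 / 0.4 | 9.6 / 4.8 | 12 |
| 0.30 | 0.9 / 0.2 | 10.8 / 2.4 | 21 |

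Example: at *p* = 0.20, 40 × 0.20 × 0.8 = 6.4 and 40 × 0.20 × 0.4 = 3.2; the difference is 100 × 0.20 × 0.4 = 8 points.

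**3. What follows**

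Incompleteness needs only *a* < 1: with 0.5 in both arms, half the events are lost and the arm difference stays at zero. Between-arm distortion needs *a*V ≠ *a*S. In the unequal rows above it makes verum look worse; reversing the attribution probabilities reverses the sign. The documents fix neither the size nor the direction.

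**The case against.** The strongest case against has four parts.

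- **The text does not say that other events go unrecorded.** Table 1 has two safety rows, and Safety Evaluation could be describing the acupuncture-specific one, with the other row covering adverse events generally. This is a possible reading, and it is why one cannot say that treatment-attributed events are the only safety data collected. It does not remove the problem. The section's adverse event sentence does not tie itself to one row, and its serious-event sentence makes relatedness the condition for CRF entry. All-cause capture is not assured on the text.
- **Bias is not shown.** A reader might infer that unblinded acupuncturists will filter events differently by arm. The documents do not say that they judge causality; they say only that they are not blinded, while participants and outcome assessors are. With equal attribution the arm difference is zero. This stands: differential capture is a risk only.
- **No verum–sham safety comparison is described.** The Objectives name none, and Clinical Data Analysis names demographic, baseline and efficacy data. A reader might infer that a planned comparison is invalid, or that the trial could support no safety statement at all. Neither is supported, and the unfiltered laboratory tests count against the second.
- **This is a condensed article.** Severity grading, assessor roles and reporting routes commonly sit in a full protocol. That is fair for those details. The point here rests on a capture rule that the article does state.

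**Conclusion.** The point holds in limited form. Safety Evaluation words adverse event recording, and serious adverse event reporting and CRF entry, as conditional on causality, and this scope is narrower than the unqualified row in Table 1. Followed as written, it gives incomplete clinical event data. That conclusion follows from the rule itself and needs no assumed rate. Laboratory safety data are unaffected.

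Differential capture is plausible, given a non-penetrating sham, unblinded acupuncturists and no named causality assessor, but it is not established. Its illustrative size, 4 to 12 points with attribution of 0.8 against 0.4 and up to 21 points at the extreme shown, rests wholly on assumed all-cause rates of 10% to 30% and assumed attribution probabilities. The serious-event sentence is the strongest reason to act, because under it a mistaken judgement of unrelatedness leaves no stated trace. The change should be made; it does not bear on the efficacy objectives.

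**What to change.** Reconcile Safety Evaluation with Table 1 so that both set the same scope:

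- Record all adverse events and all serious adverse events in both arms through week 8, regardless of presumed cause, and drop relatedness as the condition for reporting a serious event or entering it in the CRF.
- Record relatedness afterwards as a separate field, judged where possible by the outcome assessor, who is already blinded.
- If the acupuncture-specific row in Table 1 is meant as a subset of the adverse event row, say so.

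The cost is one rewritten paragraph, a CRF field for relatedness, and slightly more recording work.

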### Trial Design

This trial is designed as a randomized, sham-controlled trial with blinded participants, outcome assessor, and statistician. In this study, 80 eligible participants will be randomized to the verum acupuncture (VA) or sham acupuncture (SA) group with a ratio of 1:1. The total research period will be preceded by a 1-week run-in phase after the screening visit, then following the 4-week treatment phase, and 4-week follow-up phase. Forty healthy volunteers will also be enrolled to serve as a healthy control group. Healthy volunteers will not receive any treatment, and the correlation between gut microbiota and fecal miRNAs will be determined by comparing the constipated patients before treatment with them. The time frame of this trial is presented in Table 1.

**Table 1 T1:** Time points of treatment assessment.

	**Enrollment**	**Baseline**	**Treatment phase**		**Follow-up phase**			
**Time point**	**Week −1**	**Week 0**	**Week 2**	**Week 4**	**Week 5**	**Week 6**	**Week7**	**Week 8**

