**Figure 2 F2:**
[figure not shown]
Location of acupoints and non-acupoints.

The specific operations will be as follows: the rubber ring on the PSD base will be removed first to introduce a disposable filiform needle with the needle tip exposed. Then, the needles will be advanced at the selected acupoints, and the direction and depth of acupuncture will be strictly under the basic requirements of acupuncture operation. Following needle insertion, the needles will be modestly lifted and twirled to get local distension until *de qi* (a component sensation, including soreness, numbness, distension, and heaviness). Within 30 min, manual manipulation for each acupoint lasted 10 s and will be repeated three times with intervals of 10 min.

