#### Sham Acupuncture Group

The sham acupoints of ST25, SP14, and ST37 will be selected to perform sham acupuncture without skin penetration (Table 2 and Figure 2). We will formulate and follow the standardized step-by-step instructions and operations to use the same rituals in the VA and SA groups as far as possible. However, instead of penetrating the skin, the blunt needles will be retracted into the hollow needle handle without penetrating the skin or reaching *de qi*. The frequency and course of treatment will be the same as those in the VA group.

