#### Primary Outcome Measurement

The primary outcome will be the proportion of patients with 3 or more mean weekly complete SBMs (CSBMs) over weeks 1–4 and 5–8. The mean weekly CSBMs will be calculated by dividing the sum of the CSBMs during weeks 1–4 or 5–8 by 4. The proportion of patients with mean weekly CSBMs ≥ 3 will be divided by the number of observed participants in this group, and then multiplied by 100% (11). One SBM refers to the bowel movement that occurs in the absence of rescue medicine, or other auxiliary techniques (laxatives, suppositories usage, or manual assistance) within the preceding 24 h; while one CSBM refers to an SBM with the sensation of complete evacuation.

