### Statistical Analysis

#### Clinical Data Analysis

The statistical analysis plan will be determined before the initiation of the study. Demographic characteristics, baseline characteristics, and efficacy indicators will be analyzed using SPSS 25.0 software according to Full Analysis Set (FAS) and Per Protocol Set (PPS). The missing values in the FAS will be treated using the Last Observation Carried Forward method with the data closest to the first observation. The research results will be mainly based on the results of the FAS, and the results of PPS will be used as auxiliary references.

Continuous variables of normal distribution will be represented by 95% confidence interval, mean and standard deviation. Continuous variables of non-normal distribution will be described by median and inter-quartile range. Classification variables will be described in terms of percentage and frequency. The qualitative data will be compared using the chi-square test. If the quantitative data are normally distributed, we will use the analysis of variance to detect the difference between groups; otherwise, the Mann-Whitney test will be used. The data table will be recorded anonymously and statistical analysis will be carried out by independent statisticians who are blinded to the allocation.

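### The rule for intervention-related serious adverse events takes the participant out of the study, so outcome and safety data stop along with treatment

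*Protocol article*

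**What the plan says.** All places are in the protocol article.

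- **Safety Evaluation.** Ordinary events are to be noted: "The adverse events caused by acupuncture will be recorded, such as bleeding, pain, hematoma, syncope, local infection, and so on". The text then turns to the serious ones: "Serious adverse events related to the intervention will be reported to the key researchers and recorded in the CRF". The next sentence is the rule at issue: "Affected participants will withdraw from the study and apply for treatment or rescue promptly". From its position, the affected participants are those with a serious event related to the intervention. Blood, renal and liver tests are done in the run-in and at the end of treatment.
- **Trial Design and Table 1.** After the run-in, the schedule is "then following the 4-week treatment phase, and 4-week follow-up phase". Table 1 marks efficacy assessments, PAC-QOL and adverse events at weeks 2, 4 and 8. After enrollment, laboratory tests and the microbiota and microRNA samples are marked once more, at week 4.
- **Primary Outcome Measurement.** The count of responders "will be divided by the number of observed participants in this group".
- **Clinical Data Analysis.** Results rest mainly on the full analysis set (FAS), where missing values "will be treated using the Last Observation Carried Forward method with the data closest to the first observation".

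**The concern.** A participant can stop receiving needling and still keep a diary, complete a questionnaire, give a blood sample and report how an event resolved. The rule does not allow for that: it ends participation in the study, and nothing in the article provides for assessments afterwards. Information therefore stops for the people whose safety course matters most.

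The missing data also have a treatment-related cause. They are replaced by carried-forward values or lost from the denominator, although the real values could often have been collected. No later analysis can recover data that staff were told not to collect.

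**Working it through.** The plan states no figure on this point, so there is none to reproduce. The check has three parts.

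**1. What a withdrawn participant misses (rule set against Table 1)**

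| Time of the event | Not collected if the rule is followed as written |
|---|---|
| During treatment, after the week 2 assessment | Rest of the weeks 1–4 diary; week 4 PAC-QOL, adverse-event check, laboratory test and fecal sample; all of the weeks 5–8 diary; week 8 PAC-QOL and adverse-event check |
| After the week 4 assessments | Rest of the weeks 5–8 diary; week 8 PAC-QOL and adverse-event check |

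Data from before the event are kept in both cases.

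**2. How many participants**

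Input: 40 per arm (Calculation of Sample Size). The documents give no rate of related serious events, so the rate *r* is an assumption. Expected withdrawals in one arm = 40 × *r*; probability of at least one = 1 − (1 − *r*)^40.

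| Assumed *r* | Expected of 40 | P(at least one) |
|---|---|---|
| 0.5% | 0.2 | 0.18 |
| 1% | 0.4 | 0.33 |
| 2.5% | 1.0 | 0.64 |
| 5% | 2.0 | 0.87 |

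For comparison, the 20% drop-out allowance is 0.20 × 40 = 8 per arm.

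**3. Effect on the primary proportion**

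The responder counts here are illustrations, not figures from the plan. Suppose *k* of 40 are withdrawn and *x* of those who remain respond. The observed-participant proportion is *x*/(40 − *k*). The proportion of all randomized is *x*/40 if the withdrawn are non-responders and (*x* + *k*)/40 if they are responders.

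| *x* | *k* | Observed | All, withdrawn are non-responders | All, withdrawn are responders |
|---|---|---|---|---|
| 12 | 1 | 12/39 = 30.8% | 12/40 = 30.0% | 13/40 = 32.5% |
| 12 | 2 | 12/38 = 31.6% | 12/40 = 30.0% | 14/40 = 35.0% |
| 16 | 1 | 16/39 = 41.0% | 16/40 = 40.0% | 17/40 = 42.5% |
| 16 | 2 | 16/38 = 42.1% | 16/40 = 40.0% | 18/40 = 45.0% |

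Dropping one participant shifts the arm up by about 0.8 to 1.0 points if that person was a non-responder, and down by about 1.5 to 1.7 points if a responder. Under carrying forward, one wrong classification moves the arm by 1/40 = 2.5 points, either way. Patients enter with two or fewer complete spontaneous bowel movements per week (Inclusion Criteria), below the responder threshold of 3. A value carried from close to baseline would therefore count as non-response.

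**The case against.** **The full protocol may settle it.** A journal article usually leaves early-termination visits and follow-up of serious events to the full protocol, which is not shown. Silence on those details would be no finding. But the article is not silent: it states a rule, and the rule ends study participation. If the authors meant only that needling ends, the sentence needs correcting for that reason.

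**It would be too strong to say that follow-up of the event itself is ordered to stop.** The event is reported and recorded, and the participant is directed to care. What stands is narrower: once the participant has left the study, nothing in the article provides for the later assessments.

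**A reader might infer that the loss falls mainly on verum.** Verum needles are worked in the tissue ("Following needle insertion, the needles will be modestly lifted and twirled to get local distension until"), while in the sham arm "the blunt needles will be retracted into the hollow needle handle without penetrating the skin or reaching" that sensation. An excess in verum is plausible from this, but it is not shown. Bleeding, hematoma, syncope and local infection are listed as ordinary events to be recorded. They do not trigger withdrawal unless serious and related, and pain and syncope can occur in either arm. No rate is given for either arm.

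**A reader might also infer a bias in favor of verum.** That requires the withdrawn verum patients to be non-responders who leave the denominator. A withdrawn responder, or an early low value carried forward, moves the result the other way.

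**The analysis rules are not specific to these participants.** This is correct. The FAS is the main analysis and can retain them with filled values. Weaknesses in carrying forward or in the observed denominator affect all missing data and are separate matters. They show here only that the analysis does not restore what the rule stops collecting.

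**Conclusion.** The point holds as a defect in data collection. The rule merges stopping treatment with leaving the study, and following it loses scheduled outcome and safety data in participants harmed by the intervention. That loss occurs with a single event and depends on no assumption about arms or responder status.

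The effect on efficacy is secondary and likely small. Under assumed rates of 0.5% to 5%, 0.2 to 2.0 participants of 40 would be withdrawn, each able to move the arm by no more than about 2.5 points. The documents fix neither the direction of a bias nor an imbalance between arms, so neither should be claimed.

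The conclusion assumes that the sentence means what it says, and that no unshown document keeps these participants under assessment. It is a worthwhile, inexpensive correction and does not threaten the trial's validity.

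**What to change.** Add to Safety Evaluation, and reconcile the present sentence with it:

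> Discontinuing study treatment is distinct from withdrawing from the study. Unless consent is withdrawn, scheduled diary, PAC-QOL, laboratory and adverse-event collection continues to week 8, the event is followed to resolution, and the participant remains in the FAS denominator.

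The end-of-treatment fecal sample can be named in the same list if the participant is able and willing to give it. If the full protocol already says this, the article's sentence should be brought into line.

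The change concerns data collection only. It takes no position on when treatment should stop or how an event should be managed. The cost is a short addition to the text and continued contact with a few participants, some of whom may decline.
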